The specific aims of the TEAM-UP (Turn Everyone And Move for Ulcer Prevention) study are to:Aim 1: Determine differences in the incidence of new pressure ulcers (PrU) in nursing home (NH) residents at low, moderate, and high risk using VE support surfaces and repositioned at intervals of 2, 3, or 4 h, in nine randomly assigned NHs over a 4-week period, using the patient monitoring (PM) system to determine movement.Aim 2: Determine how medical severity components (as measured by a modified Comprehensive Severity Index [23, 24]), changes in clinically assessed risk level (low, moderate, high as measured by the Braden Scale© [25]), assigned repositioning intervals, and their interactions are associated with development of PrUs, controlling for resident demographics.Exploratory Aim: Evaluate PrU prevention intervention approaches in NH groups repositioned at 2, 3, or 4-h by: 1) comparing the intervention resource costs (VE support surfaces, PM system service/sensor use, fixed and variable labor costs for training and repositioning) and incremental cost-effectiveness ratio of cost per % reduction in PrUs, and 2) exploring staff and resident satisfaction with intervention approach.

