**Fig. 3 Fig3:**
[figure not shown]
TEAM UP study high-level components diagram and key data sources

**Table 2 Tab2:** Summary of concepts and instruments / measurements used to collect data

Concept Measured	Measures / Instrumentation	Source (Fig. 3)
Cumulative incidence of (new) PrUs for pre-intervention (baseline) period	Cumulative Incidence rate = [(# of residents with 1 or more new PrUs during a 1-month period) ÷ (# of NH residents with 3 or more day stay)] × 100; calculated monthly to establish baseline over the 12-month period before each NH intervention begins.	• MDS 3.0 • NH self-report • EMR data extract
Cumulative incidence of (new) PrUs for intervention period	Cumulative Incidence rate = [(# of residents with 1 or more new PrUs during intervention period) ÷ (# of residents participating in intervention for 3 or more days)] × 100; calculated for the full 4-week intervention period.	• MDS 3.0 • NH self-report • EMR data extract
Braden Scale©	The Braden scale is being used per protocol by participating NHs to assess resident risk for PrUs at intervention start and weekly thereafter.	• EMR data extract
Repositioning frequency	The scheduled duration of time for a resident’s pressure exposure as reflected by the 2-, 3-, or 4-h time interval at which the resident is repositioned; each NH will be randomly assigned to one of the study’s 3 arms and will use a single NH-wide repositioning frequency.	• PMS Central Server containing Monitoring Management Software
Recorded repositioning frequency	The actual time interval at which repositioning occurs, as documented by the Leaf sensor; recorded in clock time hours and minutes, 24 h per day, from start to end of resident’s participation in the 4-week intervention. Repositioning activities of residents will be captured using the Patient Monitoring System; Admission, Discharge, Transfer (ADT) feed from NHS to Monitoring System enables a match for Study ID# to resident movement, which is required for resident tracking in the event of room change, discharge/readmission, or other events.	• PMS Central Server containing Monitoring Management Software
Repositioning protocol adherence: % agreement	Percentage of agreement between scheduled repositioning frequency and repositioning frequency recorded by wireless sensor: [(scheduled clock time - recorded clock time = # minutes difference) ÷ 60] × 100]; calculated for each resident’s repositioning episode.	• PMS Central Server containing Monitoring Management Software

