Because we will be examining PrU development from assessment to assessment, the rate of PrU incidence will be modeled as a binary outcome using repeated measures logistic regression and a specified working correlation matrix that models the correlation of responses within subjects. Full likelihood estimation methods are not appropriate for repeated measures logistic regression, so generalized estimating equations (GEEs) will be used instead with model fit assessed using the quasi-likelihood information criterion (QIC). Robust standard errors, clustered at the facility level, will be employed to account for covariance among residents within facilities over time. To test the robustness of models, we will also use non-linear mixed models using PROC GLIMMIX as another option for modeling the data (instead of GEEs using PROC GENMOD). With PROC GLIMMIX, we can use random effects to model the covariance rather than clustered standard errors. As predictors, we will include time-invariant resident characteristics, e.g., age, gender, Medicaid payer, and repositioning schedule, as well as time-varying characteristics, such as resident severity measure, risk level as determined by Braden Scale© score, staffing characteristics (e.g., number, mix, and turnover), and suggested MDS resident data elements as covariates. We may lag some time-varying resident characteristics by one assessment because we want to study the associations of repositioning time with PrU development, controlling for the starting point of the resident for that assessment interval. Interaction variables will be included in the predictor data set.

Residents without PrUs who drop out of the study after at least a three-day stay but before the conclusion of 4 weeks will be included in the analysis based on intent to treat. Residents who develop a Stage 3 or worse PrU, or deep purple discoloration, will be removed from the study per repositioning protocol, but will be considered a completed case if the ulcer developed on the coccyx, sacrum, trochanter or heel. Residents who develop ulcers on sites not thought to be influenced by bed position or limited mobility, or related to sitting, will continue to be followed for analysis, but will not be included in the NH-wide protocol.

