##### Statistical power.

According to previous research, the average PrU incidence rates range from 5.2–15%. At the time of study design, the nine NHs within the NHS were identified with the highest PrU incidence rates which averaged 9.2% (SD = 3.3%). In power analyses, we used 3.5% for PrU incidence as the expected rate for intervention since it is the highest rate found in the TURN study (for moderate-risk patients). The PrU incidence rates have been translated into an odds ratio of 0.38 (= 3.5%/9.2%) as the effect size to detect. For Aim 1, odds ratios from a logistic regression of PrU incidence rates in the three treatment arms (i.e., at 2-, 3-, and 4-h repositioning frequencies), controlling for risk level, are proposed to test the difference in PrU incidence rates between the 4-h arm and the 2-h arm as well as between the 4-h arm and the 3-h arm at 4 weeks; we are assuming that the distance between the 2-h arm and the TURN 3-h odds ratio will be larger. A sample size of *N* = 951 (*n* = 317 for each arm) will be required to detect an odds ratio of .38 with a power of 0.95 at a one-tailed significance level of α = 0.05, according to G*Power. We are using a power of 0.95 instead of the conventional power of 0.80 to ensure that we will have a smaller Type II error to test the hypothesis of no-group difference that we expect to fail to reject. We are using a one-tailed test since we are only interested in determining whether the PrU rate is higher for assigned repositioning intervals longer than the current 2-h standard practice.. For Aim 2, GEE is proposed. A sample size of *n* = 114 for each group (total *N* = 342) will be required to detect an effect size of 5.7% (= 9.2% - 3.5%) with a power of 0.80 at a one-tailed significance level of α = 0.05, using the algorithms GEESIZE developed by Dahmen, et al., on an autoregressive structure for residual correlations [48]. Since the nine NHs will be randomly assigned to the three treatment arms, risk level will be the only potential covariate to be controlled in the models, and this is already considered in the power analyses. Therefore, we will target a sample size of *N* = 951 (the larger of the two required sample sizes) for both aims while taking into account potential losses due to turnover, attrition, and exclusion criteria. While this proposed study may look like a non-inferiority or equivalence trial, we will run regular one-tailed superiority tests, because (as noted earlier) we are only interested in examining whether or not the PrU rate is higher for less frequent repositioning than for the standard 2-h repositioning. (We assume that 2-h repositioning was followed to produce the 9.2% average PrU incidence rate across our 9 study NHs, because that is the current standard of care). Also, according to Snapinn [49], non-inferiority trials have many controversial assumptions and limitations that need to be made or addressed, and that is beyond the control of our study. For incidence, it is difficult to specify a non-inferiority margin for PrU rates. Instead, we will test the hypothesis of no group-difference by examining whether the 95% confidence intervals of the odds ratios (for Aim 1) or the PrU rates (for Aim 2) of the two pairs of compared groups (e.g., 4-h arm vs. 2-h arm and 4-h arm vs. 3-h arm) overlap. If the confidence intervals do overlap, the hypothesis for no-group difference will be confirmed.

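### The Aim 2 figure of 114 per group for 0.80 power does not fit the plan's 4-week cumulative outcome: 9.2% v 3.5% needs about 215 to 244 per group, and 114 gives about 0.52 to 0.58

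*Protocol article*

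**What the plan says.** The Statistical power section of the protocol article takes its reference rate from the nursing home system: "the nine NHs within the NHS were identified with the highest PrU incidence rates which averaged 9.2% (SD = 3.3"%). For the comparison rate, "we used 3.5% for PrU incidence as the expected rate for intervention". The Aim 1 calculation uses these two rates for differences between arms at 4 weeks.

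The Aim 2 calculation uses them again: "A sample size of *n* = 114 for each group (total *N* = 342) will be required to detect an effect size of 5.7"%, that difference being "9.2% - 3.5%) with a power of 0.80 at a one-tailed significance level of α = 0.05". The method is a GEE sample-size algorithm "on an autoregressive structure for residual correlations". The number of assessments, the size of the correlation and a per-assessment rate are not given. The section then adopts 951, the larger of the two requirements, for both aims.

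Table 2 defines incidence in the intervention period as the percentage of residents with at least one new ulcer, "calculated for the full 4-week intervention period". The baseline rate is defined in the same way over one month. Under Quantitative analyses, "the rate of PrU incidence will be modeled as a binary outcome using repeated measures logistic regression", from one assessment to the next. Aim 2 in the Background asks how severity, change in risk level, "assigned repositioning intervals, and their interactions are associated with development of PrUs".

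**The concern.** A cumulative incidence gives one yes-or-no result per resident. Dividing the four weeks into several assessments spreads the same events over more rows and does not create new ones. A repeated-measures formula gives a smaller sample size when every assessment carries the full contrast. That suits a condition that can be present or absent at each visit. It does not suit a 4-week incidence of 9.2% v 3.5% that is merely observed in weekly slices.

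At stake is the truth of a printed sample size and power. A reader who compares 342 with 951 would conclude that Aim 2 is provided for almost threefold (951 / 342 = 2.8). On the 4-week definition the ratio is about 1.3 to 1.5 (951 / 730 to 951 / 645), before clustering.

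**Working it through.** **Inputs.** From Statistical power: p1 = 0.092, p2 = 0.035, difference 0.057, one-sided alpha 0.05 (z = 1.645), power 0.80 (z = 0.842), n = 114 per group, planned 317 per arm. From Table 2: one cumulative outcome per resident. Assumption: 9.2% is a rate over about four weeks. The power section does not give its period. The reading rests on the use of both rates at 4 weeks in Aim 1 and on the one-month and 4-week definitions in Table 2.

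**1. Can 114 be reproduced?** Not from the printed inputs alone. With one outcome per resident, the unpooled formula gives

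n = (1.645 + 0.842)² × (0.092 × 0.908 + 0.035 × 0.965) / 0.057² = 6.183 × 0.1173 / 0.003249 = 223.

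For T assessments with first-order autoregressive correlation rho and the same 9.2% v 3.5% at each, n is multiplied by the mean of the T × T correlation matrix:

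| T | rho | multiplier | n per group |
|---|---|---|---|
| 4 | 0.5 | 8.25 / 16 = 0.516 | 115 |
| 4 | 0.493 | 0.511 | 114 |
| 3 | 0.341 | 0.511 | 114 |
| 5 | 0.585 | 0.511 | 114 |

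Several pairs reach 114, so agreement shows only that this route is possible.

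**2. Size and power with one 4-week outcome per resident**

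| Method | n per group for 0.80 | Power at 114 | Power at 317 |
|---|---|---|---|
| Unpooled z | 223 | 0.55 | 0.91 |
| Pooled z | 225 | 0.55 | 0.90 |
| Log-odds Wald | 244 | 0.52 | 0.88 |
| Arcsine | 215 | 0.57 | 0.92 |
| Exact enumeration of the pooled z test | 218 | 0.58 | 0.92 |

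For example, the unpooled power at 114 is Φ(0.057 / √(0.1173 / 114) − 1.645) = Φ(1.777 − 1.645) = Φ(0.132) = 0.55. In total, 3 × 215 = 645 and 3 × 244 = 732, so about 645 to 730. Two other methods fall outside the power range at 114 without changing the picture: Fisher's exact test gives 0.44, and a log-rank approximation gives 0.60. The expected number of events in two groups of 114 is 114 × (0.092 + 0.035) = 14.5.

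**3. Do weekly assessments help?** Weekly risks that accumulate to the stated rates are 1 − 0.908^(1/4) = 2.4% and 1 − 0.965^(1/4) = 0.9%. A simulated weekly model with follow-up ending at the first ulcer gives power 0.53 (Wald) to 0.57 (score) at 114, and nearly the same with one, two or five intervals. If every resident instead stays at risk in all four weeks, there are 4 × 114 = 456 resident-weeks per group and the power is about 0.56.

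**4. Could 9.2% and 3.5% be weekly rates?** With four weekly assessments, correlation 0.5 and a first-order Markov chain, the 4-week incidences would be 1 − 0.908 × (0.908 + 0.5 × 0.092)³ = 21% and 1 − 0.965 × (0.965 + 0.5 × 0.035)³ = 8.5%. That does not agree with the use of the same two figures at 4 weeks in Aim 1, and 21% lies above the 5.2% to 15% that the section cites from earlier research.

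**The case against.** The strongest reply is that 342 decides nothing. The trial is sized at 951, and the corrected total of about 645 to 730 is still smaller. Power at 317 per arm is 0.88 to 0.92 before clustering, above the 0.80 planned for Aim 2. That stands, and it limits the point to a misstated figure. A reader might go further and infer that the trial is too small or that 951 must change. This point does not show that.

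A reader might also take it as proven that the calculation counted the 4-week incidence anew at each assessment. The documents do not support that. The number of assessments and the correlation are not printed, an article may leave them to the full protocol, and with the correlation free a match to 114 can be found for three, four or five assessments. The shortfall at 114 does not depend on the cause.

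It can be said too that Aim 2 concerns ulcer development from assessment to assessment, and that some residents stay under follow-up after an ulcer, so repeated outcomes are not excluded. That is fair as to the model. It does not rescue 114, because weekly risks consistent with the stated rates give about 0.56 even when nobody leaves the risk set.

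Finally, a reader might infer that the interactions in Aim 2 cannot reach 0.80 power at 951. That depends on assumed patterns. If the whole effect lies in one risk stratum holding 20% to 57% of residents, with no difference elsewhere, log-odds power at 317 per arm is about 0.29 to 0.49. If the effect reverses in the other stratum, an extreme case, it is 0.83 to 0.88 for shares of 30% to 57%. The plan claims no power for interactions. All that can be said is that its calculation sizes none.

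**Conclusion.** The statement that 114 per group gives 0.80 power for Aim 2 is wrong for the outcome as the article defines it. The requirement is roughly twice as large, and the power at 114 falls short by about 22 to 28 percentage points. The conclusion rests on reading 9.2% and 3.5% as cumulative rates over about four weeks and on independence between residents. Clustering by home would lower every power figure here. With three homes per arm, a design effect of 1 + (m − 1) × ICC and assumed ICCs of 0.005, 0.01 and 0.02, pooled-z power at 317 per arm would be 0.77, 0.66 and 0.51. The article gives no ICC, and clustering is a separate matter. The correction should be made, but no change to the target of 951 follows from this point alone.

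**What to change.** Replace the 114 / 342 / 0.80 statement with a calculation on the 4-week cumulative outcome. Alternatively, keep the GEE algorithm with per-assessment rates that accumulate to 9.2% and 3.5% (about 2.4% and 0.9% for four weekly assessments), and state the number of assessments and the correlation. Report about 215 to 244 per group for 0.80 power, naming the formula used, and about 0.88 to 0.92 at the planned 317 per arm, both before clustering. Add that these figures refer to the contrast between arms and that no interaction has been sized.

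The cost is one recalculation and a few reworded sentences. No residents are added on this account. The Aim 2 requirement will look less favourable than it does now.

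### The power stated for Aim 2 covers at most an arm contrast, not the severity, risk-change and interaction terms that define the aim

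*Protocol article*

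**What the plan says.** **Sizing (Statistical power).** Aim 2 will use GEE. The required size is 114 per group (342 in total), for an "effect size of 5.7% (= 9.2% - 3.5%) with a power of 0.80 at a one-tailed significance level of α = 0.05", calculated "on an autoregressive structure for residual correlations". The article then argues that, because homes are randomised, "risk level will be the only potential covariate to be controlled in the models, and this is already considered in the power analyses". On that basis N = 951, the larger of the two computed sizes, is adopted for both aims.

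**The question (specific aims, end of Background).** Aim 2 asks how severity components, changes in risk level, "assigned repositioning intervals, and their interactions are associated with development of PrUs, controlling for resident demographics".

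**The model (Quantitative analyses).** The GEE paragraph states: "As predictors, we will include time-invariant resident characteristics, e.g., age, gender, Medicaid payer, and repositioning schedule, as well as time-varying characteristics". The time-varying list names severity, Braden risk level, staffing (number, mix, turnover) and MDS items. It adds: "Interaction variables will be included in the predictor data set". The opening paragraph of the same section names interactions of severity change and risk change with the repositioning schedule.

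**Facility data (NH-level data).** Home characteristics and facility-level figures are also to be covariates in the multivariate analyses.

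**The concern.** The power section describes a model with the arm and one covariate. The aims and analysis sections describe a model in which the arm main effect is only one of several targets, with a much longer covariate list. A reader who takes the power section at its word would believe that Aim 2 has power 0.80 for its own question. The figure was calculated for a different question.

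The justification offered does not close the gap. Randomising homes bears on confounding of the arm contrast. It does not make severity, change in risk level or their interactions with the interval unnecessary, because those terms are what Aim 2 sets out to study.

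At stake is what a null Aim 2 result can support. If an interval-by-risk or interval-by-severity interaction is not significant, and the plan appears to carry power 0.80 for it, the result can be taken as evidence that the interval makes no difference at that risk or severity level. The trial may have had less than an even chance of detecting such a difference.

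**Working it through.** **1. The plan's own figure.** Inputs from Statistical power: p1 = 0.092, p2 = 0.035, one-tailed α = 0.05, power 0.80.

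Single-wave comparison of two proportions, unpooled variance:

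n = (z0.95 + z0.80)² × [p1(1−p1) + p2(1−p2)] / (p1−p2)² = 6.183 × (0.0835 + 0.0338) / 0.057² ≈ 223 per group (226 with pooled variance under the null).

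The stated 114 is lower because the method uses repeated measures. The article gives neither the number of waves nor the correlation, so 114 cannot be reproduced from the stated inputs alone. It can be reached with assumed values. With 4 waves and AR(1) correlation 0.5, the variance factor for the mean is [4 + 2(3×0.5 + 2×0.25 + 0.125)]/16 = 0.516, and 223 × 0.516 ≈ 115. So 114 is plausible for an arm main effect. Nothing in the calculation refers to severity, change in risk or an interaction.

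**2. The arm contrast at 317 per arm.** Under the same single-wave comparison without clustering:

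z = (0.057√317 − 1.645√(2 × 0.0635 × 0.9365)) / √0.1173 = (1.015 − 0.567)/0.3425 = 1.31, so power is about 0.90.

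**3. Expected residents with a new ulcer.**

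| Scenario at N = 951 | Calculation | Residents |
|---|---|---|
| All arms 3.5% | 951 × 0.035 | 33.3 |
| One arm 9.2%, two arms 3.5% | 317 × (0.092 + 0.035 + 0.035) | 51.4 |
| All arms 9.2% | 951 × 0.092 | 87.5 |
| All arms 15% (upper end of cited prior range) | 951 × 0.15 | 142.7 |

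**4. Illustrative power for an arm-by-risk interaction.** Assumptions: two arms of 317; two risk strata; the planned odds ratio applies in one stratum and the odds ratio is 1 in the other; one record per resident; no home clustering; Wald test, one-tailed α = 0.05.

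SE² = Σ 1/[n p (1−p)] over the four arm-by-stratum cells; power = Φ(|ln OR|/SE − 1.645).

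*Equal strata, base 9.2%, OR 0.38.* The affected cell has p = 0.0371. SE² = 3/(158.5 × 0.092 × 0.908) + 1/(158.5 × 0.0371 × 0.9629) = 0.227 + 0.177 = 0.403, SE = 0.635. |ln 0.38| = 0.968, so z = 1.52 and power = Φ(−0.12) = 0.45.

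*Equal strata, base 3.5%, OR 2.63 (1/0.38).* The affected cell has p = 0.0871. SE² = 3/(158.5 × 0.035 × 0.965) + 1/(158.5 × 0.0871 × 0.9129) = 0.560 + 0.079 = 0.640, SE = 0.800. z = 0.967/0.800 = 1.21 and power = Φ(−0.44) = 0.33.

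*Affected stratum one quarter of residents.* The same formula gives 0.34 and 0.29.

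*High-risk share 56.5%* (middle of the 56–57% quoted under Significance for earlier nursing-home populations). At base 9.2% the power is 0.46.

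As precision, with equal strata, the 95% interval for the interaction odds ratio spans a factor of exp(1.96 × 0.635) ≈ 3.5 either way at a base rate of 9.2%, and exp(1.96 × 0.800) ≈ 4.8 at 3.5%.

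**The case against.** **The conflict is only wording.** The article never claims power for an interaction, and the final covariate list is normally settled in the SAP. That is true of the list. But the article does make a positive statement about which covariates the models contain and that the power analyses allow for them, and its other sections contradict it. The statement cannot be confined to Aim 1. It follows the Aim 2 sizing, speaks of models in the plural, and leads to the size for both aims.

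**Aim 2 runs at 951, not 342.** This stands, and it helps the arm main effect (about 0.90 in step 2, before clustering). It supplies no figure for the other terms.

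**Exploration is already signalled.** The Background speaks of exploring risk and severity individually and in combination. This stands in part, but Aim 2 itself is worded as a determination and has a formal power figure.

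**The illustration is one choice among many.** This also stands. The effect pattern and split are assumed, and the trial's eligible Braden range may give another risk mix. The calculation also uses one record per resident instead of the planned assessment-to-assessment GEE.

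**Stronger readings that the article does not support.**

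- *That the planned model cannot be fitted.* Full coding of arm, risk, four severity levels, three demographics and all two-way interactions among the first three gives 26 parameters, and many simulated fits then separate. But the article does not say that all terms enter one fit. It names interactions with the repositioning schedule, and it also describes severity as a calculated score. Under an assumed severity mix and slopes, dropping the risk-by-severity terms cut separation at a 9.2% rate from 37% to 11% of simulated trials; at 3.5% it stayed high (98% to 90%). These figures illustrate assumed coding and are not properties of the plan.
- *That the plan will declare a null interaction to be no difference.* Its interval-overlap rule concerns pairs of arms, not interactions.
- *That 114 per group is wrong.* Step 1 does not show this.
- *That 87 is a ceiling on events.* The article also cites incidence up to 15%, and does not say that every resident leaves the repeated-measures model after a first lesser ulcer.

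**Conclusion.** The concern holds in a limited form. The Statistical power section misdescribes the Aim 2 model, and its 0.80 applies at most to an arm main effect. The contradiction rests on the article's text alone. The event range of about 33 to 87 follows from its planning rates and N = 951. Deleting residents with missing data, as the Missing data section allows, could lower it.

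The interaction power of about 0.3 to 0.45 is illustrative and depends on the assumptions in step 4. Home clustering is left out. It would lower the arm-contrast figure. Its effect on the interaction depends on how far the risk gradient differs between homes, on which the article gives nothing. Interactions smaller than the full planned odds ratio would have less power.

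**What to change.** 1. Correct the sentence in Statistical power so that it agrees with the specific aims, NH-level data and Quantitative analyses.
2. State that the Aim 2 size and its 0.80 refer to the arm contrast only.
3. Give approximate power or expected precision for the interval-by-risk and interval-by-severity interactions at 317 per arm, with the assumed base rate, effect pattern, risk split and treatment of clustering.
4. Report those interactions as exploratory estimates with confidence intervals, and say that a null interaction will not be read as no difference in that subgroup.
5. Keep the time-varying risk and severity terms and the facility-level clustering of the planned GEE, since Aim 2 depends on them. Limit the interactions fitted together to what the expected events support, for example one at a time with risk and severity entered as scores (2 degrees of freedom each across three arms).

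The cost is wording and one restated calculation, with no extra residents or data. The Aim 2 interactions become exploratory, the stated power looks less favourable, and scoring risk and severity assumes a trend across levels.

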### Data collection & storage (see Fig. 3 and Table 2)

#### Quantitative data collection procedures

##### NH-level data.

NH Company has agreed to provide each participating NH’s characteristics, including bed size and nursing staff hours, facility-level data (PrU period prevalence and incidence, staff number, mix, and turnover) at baseline (12 months prior) and during the intervention period. Staff mix, wage, and fringe benefit rates will be also be obtained. Data will be collected from publicly available sources (https://www.medicare.gov/nursinghomecompare/search.html). These data will be used as covariates in the multivariate analyses.

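### Risk level is made the only covariate because nine homes are randomised; three homes per arm cannot be relied on to balance home-level PrU rates, and other sections of the protocol contradict the restriction

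*Protocol article*

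**What the plan says.** Four places in the protocol article bear on the covariates of the arm comparison.

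- **Statistical power.** Aim 1 is a logistic regression on the three arms that controls for risk level and tests 4 h against 2 h and 4 h against 3 h. From the random allocation of the homes the section then infers that "risk level will be the only potential covariate to be controlled in the models". This follows the sample-size statements for both aims and is not limited to either.
- **NH-level data.** Each home's size, staffing and PrU prevalence and incidence are obtained for the 12 months before the intervention and during it. The section closes: "These data will be used as covariates in the multivariate analyses". It names no aim.
- **Table 2.** Pre-intervention cumulative PrU incidence is "calculated monthly to establish baseline over the 12-month period before each NH intervention begins".
- **Quantitative analyses.** The GEE and GLIMMIX models of PrU incidence take age, gender, payer, severity, Braden risk, staffing and MDS items as predictors. Baseline home PrU incidence is not in that list.

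The Methods section puts three homes in each arm and describes no matching or stratification on baseline incidence.

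**The concern.** Randomisation makes the arm contrast unbiased on average over all possible allocations. It does not make any one allocation of nine homes balanced. The interval is assigned to whole homes, so the contrast is in effect a comparison of three home means with three others. If one arm happens to draw homes with higher underlying rates, the difference enters the result directly. Resident-level adjustment for Braden category removes only the part of it that risk level explains.

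Two things are at stake. A 4-h arm could look safe or harmful because of the homes it drew. And the protocol gives two incompatible answers on which covariates enter its main comparison, so the choice could be made after the results are seen. The decision rule adds weight: overlapping confidence intervals are to be read as confirming no difference, so avoidable between-home noise pushes towards declaring the longer interval acceptable.

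**Working it through.** **Inputs, all from Statistical power unless noted.** Mean home incidence 9.2% with SD 3.3 points, given for the nine homes identified at design and taken here as the between-home SD. Expected rate 3.5%: "we used 3.5% for PrU incidence as the expected rate for intervention". Target difference 9.2 − 3.5 = 5.7 points, stated for Aim 2 from the same two rates that Aim 1 uses. Three homes per arm (Methods).

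**The plan's own figure.** The plan gives N = 951 "to detect an odds ratio of .38 with a power of 0.95 at a one-tailed significance level of α = 0.05". Standard logistic-regression sample-size formulas with a base rate of 9.2%, odds ratio 0.38 and a binary predictor covering one third or two thirds of the sample give 947 to 964. So 951 reproduces as a total for independent residents, and between-home variation does not enter it.

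**Chance gaps in underlying home rates, with no interval effect.**
- SD of the difference between two arm means: 3.3 × √(1/3 + 1/3) = 2.69 points.
- Mean absolute gap for one named pair: 2.69 × √(2/π) = 2.15 points; 2.15/5.7 = 38%.
- Probability that this gap exceeds half the target (2.85 points): 2 × [1 − Φ(2.85/2.69)] = 0.29.
- Larger of the two contrasts that Aim 1 tests (simulation): mean 2.93 points, 51%.
- Largest of the three arm-to-arm gaps: 1.693 × 3.3/√3 = 3.2 points, 57%.

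Listing all 1,680 ways to allocate nine homes to three arms, under three assumed shapes for the home rates, gives 39–40%, 52–55% and 58–60% for the last three gap sizes (one pair, larger of two, largest of three).

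**Sampling noise inside the 3.3.** The true SD is √(3.3² − 100² × 0.092 × 0.908/n), where n is the assumed number of residents behind each home's rate.

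| Assumed n | True SD | One pair, % of target | Largest gap, % of target |
|---|---|---|---|
| 106 | 1.7 | 20 | 30 |
| 317 | 2.9 | 33 | 49 |
| 1,200 | 3.2 | 36 | 55 |

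**What a home-level baseline term would buy.** This is a home-level comparison of 4 h with 2 h: effect 5.7 points, one-sided 0.05, 9 − 3 = 6 degrees of freedom unadjusted (critical t 1.943) and 5 adjusted (2.015). With 3.3 as the whole home-level variation, unadjusted power is about 0.59. Adjusted power depends on the assumed correlation between baseline and trial-period home rates:

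| Correlation | 0.3 | 0.5 | 0.6 | 0.7 |
|---|---|---|---|---|
| Power | 0.54 | 0.61 | 0.67 | 0.75 |

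Break-even is near 0.45.

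Now add binomial noise for a four-week rate on about 951/9 = 106 residents: 100 × √(0.092 × 0.908/106) = 2.8 points. If the true SD is 3.3, the observed rates have SD √(3.3² + 2.8²) = 4.3. Power is then about 0.41 unadjusted and 0.45 adjusted at a true correlation of 0.7. If the true SD is only 1.7, there is no gain even at 0.7.

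**The covariate statements side by side.** Statistical power allows one covariate. NH-level data promises home-level covariates including baseline incidence. Quantitative analyses lists many resident and staffing predictors. These cannot all describe the same models. The home-level items named (bed size, nursing hours, PrU prevalence, PrU incidence, staff number, mix, turnover) are seven. If each entered as one value per home, they would exceed the six available degrees of freedom.

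**The case against.** The strongest reply is that the protocol does not settle the exclusion of baseline incidence. The restrictive sentence sits in a power paragraph, while NH-level data says these data will be covariates. This stands. A reader might infer that baseline PrU incidence is definitely left out of Aim 1; the documents support only a contradiction.

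A reader might also infer that chance gaps typically exceed half the target effect. That is true of the largest of the three gaps and, barely, of the larger of the two tested contrasts. For the named 4-h v 2-h contrast the average is 38%.

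It can also be said that adjustment may not help. This stands too. The correlation is not documented, four-week rates are noisy, and the denominators differ: Table 2 counts all residents with a stay of three or more days at baseline but only intervention participants during the trial. The upper part of the power range may be out of reach.

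Finally, the facility-clustered standard errors in Quantitative analyses are meant to carry between-home variation into the uncertainty. They do not remove an imbalance that has occurred, and they do not make the balance argument correct.

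**Conclusion.** The point holds in two parts. First, randomising nine homes is not a valid reason to treat risk level as the only covariate: on the plan's own SD, the 4-h v 2-h chance gap has SD 2.7 points and averages 2.15 points, 38% of the 5.7-point target. Second, the covariate statement conflicts with two other sections, so the Aim 1 model is not fixed.

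The sizes rest on reading 3.3 as a between-home SD that carries over to the trial. It describes homes picked at design for high incidence, whereas the NH sample section describes a convenience sample of volunteers, and part of it is sampling noise. The per-contrast average could be as low as 20% of the target under the smallest assumed n.

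This should be corrected, but it does not invalidate the randomised comparison. The case for a home-level baseline term rests on fixing the model in advance and guarding against a realised imbalance; a power gain is possible but not assured.

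**What to change.** 1. In Statistical power, delete the argument that randomising nine homes leaves risk level as the only covariate.
2. Reconcile that section with NH-level data and Quantitative analyses: state which covariates enter the Aim 1 model and which belong only to the Aim 2 models.
3. Specify Aim 1 as arm, baseline risk level and one home-level covariate: the home's PrU incidence over the 12 months before launch.
4. Report the model without the home-level term as a sensitivity analysis.

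The covariate should be fixed before any outcome comparison, with no rule that keeps or drops it on the data. A rule based on an observed correlation would be unreliable: with nine homes, an observed value of 0.45 has a 95% interval of about −0.31 to 0.86.

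The cost is wording, since the data are already to be collected. The statistical price is one of six home-level degrees of freedom and a small loss of power (for example 0.59 to 0.54 at a correlation of 0.3) if baseline rates predict poorly.
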